### Data management

All activities undertaken by the Midlands and North West Bowel Cancer Screening Hub are covered by National Information Governance Board (NIGB, formerly the Patient Information Advisory Group, PIAG) approvals with regard to the handling of patient-identifiable data (Ref: PIAG 1-08(a)/2003).

No patient identifiable data will be seen by researchers outside of the screening Hub prior to consent for participation in the qualitative phase of the study. Any patient information (name, address) supplied by patients when returning a reply slip to the University of Birmingham indicating their willingness to participate in a semi-structured interview will be managed by the research staff with established procedures to ensure the confidentiality of those data and in accordance with applicable national and/or local regulations on personal data protection.

### Data monitoring

Although adverse events are not anticipated as part of this feasibility trial, it is possible that the intervention may increase the number of patients contacting the screening Hub in order to opt out of participation in any future rounds of bowel cancer screening. The Hub will inform the research team, at the end of the trial, of those individuals (anonymised, unique identifier only) who had contacted them to decline bowel cancer screening subsequent to receipt of the intervention.

An independent Data Monitoring Committee (DMC) will be formed to oversee the conduct of the trial, and will meet at regular intervals during the study. The DMC will comprise a statistician, a clinician, and a Specialist Screening Practitioner (SSP), and will evaluate interim outcomes and analyses to determine whether the study should be stopped for any reason.

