### Control Group

Patients randomised to the control arm of the trial will receive no additional contact (current standard practice).

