### Outcome collection

13 weeks after initial contact (i.e. when an individual's screening episode is due to close), the Hub will log the number of FOBt kits returned by individuals in the intervention and control arms of the trial, and return anonymised lists of patients, denoted by a unique identification number, to the University of Birmingham for analysis. The member of hub staff collecting the outcomes data will be blinded to randomisation group to avoid bias.

Participating general practices will be asked to record prospectively all patient consultations about bowel cancer screening during the trial. In order to determine the relative effectiveness of retrieving information on consultations where screening was discussed from routine GP records (i.e. compared to prospective recording by the GP), a retrospective analysis of routinely collected GP records will be carried out in two of the participating practices. When the trial has ended, the screening Hub will produce a list of all patients who had been randomised within these two practices. Practice staff will be asked to inform the research team of the number of consultations relating to bowel cancer screening that have been carried out for these patients.

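### The possible rise in opt-outs, the one harm the protocol names, is to be counted only among people who received the intervention, so no increase over background can be estimated

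*Protocol article*

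**What the plan says.** The Data monitoring section of the protocol article does not anticipate adverse events but makes one exception: "it is possible that the intervention may increase the number of patients contacting the screening Hub in order to opt out of participation" in later rounds. It then describes a single flow of data. At the end of the trial the Hub will give the research team the anonymised identifiers of those "who had contacted them to decline bowel cancer screening subsequent to receipt of the intervention".

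Under Control Group: "Patients randomised to the control arm of the trial will receive no additional contact (current standard practice").

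The second paragraph of Data monitoring sets up an independent Data Monitoring Committee (DMC) that "will meet at regular intervals during the study" and "will evaluate interim outcomes and analyses to determine whether the study should be stopped for any reason".

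Opt-outs are not among the outcomes listed under Outcome measures, and the Analysis section does not mention them. For kit returns, by contrast, Outcome collection names both arms.

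**The concern.** The stated worry is comparative: that the intervention raises the number of opt-outs. The count is not comparative, because its definition depends on having received the intervention and only one arm does.

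This is not a detail that can be left to a statistical analysis plan. The protocol fixes which people the Hub will report. If the Hub follows that text, no later analysis can recover the control figure from what it returned.

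At stake is how the result will be read. A one-arm count can mislead in two directions: opt-outs that would have happened anyway may be taken as harm, or a real excess may be dismissed as background. Patients are randomised without consent, and the result bears on whether a definitive trial follows, so the one foreseen harm should be measured in a way that can be interpreted.

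**Working it through.** **Step 1. Who can enter the count?**

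| Item | Intervention arm | Control arm | Section |
|---|---|---|---|
| Contact after randomisation | GP letter and duplicate kit | None | Intervention Group; Control Group |
| Date of receipt exists | Yes | No | follows from the row above |
| Kit returns logged at 13 weeks | Yes | Yes | Outcome collection |
| Opt-outs reported | Yes | Not described | Data monitoring |

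The quantity of interest is p(intervention) − p(control). The plan supplies a numerator for the first term and nothing for the second.

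**Step 2. Check the formula on the plan's own figure.** The protocol gives no figure for opt-outs, so the check uses the Sample size section: 3.2% against 6.4%, 90% power, 5% significance, 934 per arm. With pooled variance under the null and a two-sided test:

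n = [1.96·√(2·p̄(1−p̄)) + 1.2816·√(p1(1−p1) + p2(1−p2))]² / (p2−p1)²

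With p̄ = 0.048 this gives 936. The unpooled version gives 933. The stated 934 is reproduced. This only confirms that the formula suits the plan; the point itself rests on the reading in Step 1.

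**Step 3. What would counting both arms allow?** Inputs: 2,190 per arm (Sample size) and two-sided 5%. The control opt-out rates are assumptions, because the protocol states none.

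Power = Φ[(d − 1.96·SE0)/SE1], where d = p2 − p1, SE0 = √(2·p̄(1−p̄)/2190) and SE1 = √((p1(1−p1) + p2(1−p2))/2190).

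Example, 1% against 2%:
- p̄ = 0.015
- SE0 = √(0.02955/2190) = 0.003673
- SE1 = √(0.0295/2190) = 0.003670
- (0.01 − 1.96 × 0.003673)/0.003670 = 0.763, and Φ(0.763) = 0.777

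In the table, expected counts are the rate × 2,190, and the 95% half-width is 1.96·SE1.

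| Control rate (assumed) | Doubled rate | Expected opt-outs, control / intervention | Power for a doubling | 95% half-width of the difference |
|---|---|---|---|---|
| 0.1% | 0.2% | 2 / 4 | 13% | 0.23 points |
| 0.5% | 1% | 11 / 22 | 48% | 0.51 points |
| 1% | 2% | 22 / 44 | 78% | 0.72 points |
| 2% | 4% | 44 / 88 | 97% | 1.01 points |

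The smallest intervention rate detectable with 80% power is 0.60%, 1.30%, 2.04% or 3.37% for control rates of 0.1%, 0.5%, 1% or 2%. The normal approximation is rough in the first row, where only a handful of events is expected.

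**Step 4. Are the control data available?** The third exclusion criterion removes people who have already asked the Hub not to send them screening information or kits, so the Hub holds such requests. The Randomisation section gives every participant a unique identifier. Trial Status says recruitment had not begun. A count in both arms therefore looks feasible.

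**The case against.** The best counter-argument is that background opt-out among controls may be close to zero. Their screening episode is closed, they became non-responders one to seven months earlier, invitations come every two years, and people who had already asked for no contact are excluded. If so, the intervention-arm count nearly equals the excess and little is lost. This is plausible, and it is why no background rate should be asserted here. But it is itself an assumption, and the control count is what would confirm it.

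A second argument is that at low rates the comparison has little power, and that opt-outs are only a monitoring item in a feasibility study. That stands. It supports a descriptive estimate with an interval rather than a formal test. It does not support leaving out one arm.

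Three stronger readings may tempt a reader, and the protocol does not support them:

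- *That opt-outs are collected only at the end, so the DMC cannot act on them.* The text fixes when the Hub reports to the research team. It does not say when requests are recorded, and it does not bar the Hub from supplying the DMC. Interim outcomes are not defined, and what a DMC sees is commonly set out in a charter or full protocol that is not shown. All that can be said is that no interim supply of opt-outs is described.
- *That each opt-out cancels a returned kit, so that a given rise offsets a share of the planned 3.2-point gain.* Everyone randomised has just left an invitation and a reminder unanswered, so an opt-out need not remove a future participant. The protocol gives no basis for the exchange.
- *That the retrospective consultation count in two practices has the same defect.* Its stated purpose is to compare routine records with prospective recording by GPs. It does not claim to yield an incremental cost by arm.

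**Conclusion.** The point holds in a limited form. As described, the opt-out report covers the intervention arm only, so an increase over background cannot be estimated whatever the background rate is. This follows from the text and needs no numerical assumption.

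How much a count in both arms would show does depend on the unknown control rate. For a doubling, power runs from about 13% at 0.1% to about 97% at 2%, and those rates are assumptions. At the lower end the result would be an estimate with a wide interval. The timing of reports to the DMC is a secondary matter of clarification and not a demonstrated fault. The change is worth making before recruitment because it is cheap and makes the one named harm estimable.

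**What to change.** 1. In Data monitoring, have the Hub report opt-outs by unique identifier for all randomised patients in both arms. Count them from a common start date, either randomisation or the practice's mailing date, over the same 13-week window.
2. Present the difference between arms with a 95% confidence interval as a descriptive harm measure, and state that no firm test is intended if events are few.
3. State that the same counts by arm go to the DMC at its meetings. The text does not prevent this now, so the sentence only makes it explicit.

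The cost is a wider query on data the Hub already holds and a few lines of protocol text. No additional contact with patients is needed, and the sample size does not change.

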### Ethical considerations

Ethical approvals have been obtained from South Birmingham Research Ethics Committee (Ref: 11/WM/0086), and R&D approvals have been obtained from University Hospitals Coventry and Warwickshire NHS Trust, Coventry Teaching Primary Care Trust and Birmingham and the Black Country RM&G Consortium Trusts (CSP Ref: 63560).

#### Consent to participate

Patients will be randomised without seeking consent. This approach is being taken to avoid the likely bias in screening uptake subsequent to the intervention that would result if participants were made aware of their involvement in the research study. Seeking consent from individuals identified as non-responders by the Hub would itself be an intervention; it would be impossible to ascertain whether any difference in uptake between the control and intervention arms was due to screening participation being prompted by an approach seeking consent for inclusion within the study, or because of the effect of the GP endorsed reminder and duplicate FOBt kit.

Written informed consent will be obtained from all participants in the qualitative phase of the study prior to interview.

## Discussion

There is a lack of evidence to support the implementation of effective interventions to reduce the burden of CRC by reducing delays in diagnosis or improving participation in screening. It is estimated that there would be 20,000 fewer deaths over the next 20 years if bowel cancer screening had an uptake of 60% [29]. The success and cost-effectiveness of the NHSBCSP depends on the achievement and maintenance of high screening uptake rates in the target population, and the development of feasible, acceptable and cost-effective strategies to improve compliance with bowel cancer screening offers the opportunity to improve programme delivery and to target population sub-groups who currently underuse the service.

If the intervention proves effective in the feasibility work, we envisage undertaking a definitive trial, which will be designed and powered based on the findings of the feasibility study. It is envisaged that the definitive trial may compare Hub and GP endorsement of bowel screening, with and without the inclusion of a duplicate FOBt, to determine the relative importance of different components of the intervention. It would also establish the cost-effectiveness of the intervention for different sub-groups, and assess the suitability of the intervention being rolled out nationally within the NHSBCSP.

## Trial Status

At the time of manuscript submission, recruitment to this trial had not yet begun.
